#### Plans to promote participant retention and complete follow-up {18b}

Protocol deviations are documented on a separate list. The patients have been informed of the value of completing the study course. The patients receive reminding phone calls if they miss an acupuncture treatment or a questionnaire has not been returned in time. If a patient drops out of treatment, it will be documented on a special study discontinuation form, and the patient will be motivated to continue to complete the questionnaires. After receipt of the final questionnaire, the patients will be reimbursed for transportation fees to the study site for the 12 acupuncture sessions and 2 follow-up examinations with the lump sum of 60€.

#### Data management {19}

After checking for completeness and quality, the data will be entered in electronic databases by designated staff at the main study center at the Charité University Hospital. In a separate step, the correct transfer (e.g., double entries and range checks of the data values) and coding of the data will be checked by a different set of people. All data are archived in a standardized way and will be deleted after 10 years. The reference procedures are provided in the protocol and are consistent with the standard operation procedures of the investigating institute of the Charité University Hospital.

#### Confidentiality {27}

The study data are documented and archived using pseudonyms. During the study, all personal information will be stored in a locked, password-accessible MS-ASSESS database. Paper forms containing personal information are locked in a metal cabinet and will be destroyed along with the deletion of electronic information after the completion or discontinuation of the study. The concept of data safety had to be presented to the university responsible for data safety and follows the standards of the German legal guidelines for data safety and the Federal State of Berlin.

#### Plans for the collection, laboratory evaluation, and storage of biological specimens for genetic or molecular analysis in this trial/future use {33}

No biological specimens will be collected.

### Statistical analysis

#### Sample size {14}

A sample size of 90 patients (45 per group) will provide 80% power to detect a difference in the mean values between the acupuncture group and the control group of at least 15 mm on the VAS (DPN-related overall complaints) after 8 weeks with an anticipated common standard deviation of 25 mm using a 2-sided *t* test with a level of significance of alpha = 0.05. To account for a dropout rate of approximately 15%, 110 patients must be randomized.

#### Statistical methods for the primary and secondary outcomes {20a}

The changes in the overall number of DPN-related complaints (measured by the VAS) between baseline and week 8 will be used as the primary outcome parameter. The primary analysis of the primary endpoint will be conducted with an analysis of the covariance (ANCOVA). The treatment group (acupuncture/control) and study center will be included as fixed-effect factors in the model, and the baseline value of the overall number of VAS-DPN-related complaints will be used as a fixed covariate. The adjusted means will be derived from this model and presented along with the two-sided 95% confidence intervals in each treatment group and the *p* value of the group comparison (significance level of 5%, two-sided). The calculation will be performed using the full analysis set (FAS) based on the intention-to-treat-principle (ITT), thus evaluating each patient in the treatment group at random without the replacement of missing values. All further analyses will be considered exploratory (without adjustment for multiple testing).

The secondary outcomes will be analyzed similarly with an ANCOVA or logistic regression (depending on the scale of the outcome) and will include the treatment group and study center as fixed-effect factors and the respective baseline value (where applicable) as a fixed covariate.

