## Methods: participants, interventions, and outcomes

### Study setting {9}

This study is being conducted in Germany. The main recruiting center is located in Berlin at the Charité University Hospital, and another recruiting center is located in Hamburg in a research and treatment center for traditional Chinese medicine. The overall study duration per patient is 24 weeks. After randomization at baseline, the patients in the acupuncture group will undergo 12 treatment sessions in addition to routine care during the first 8 weeks of the study, followed by 16 weeks of follow-up. In the control group, all patients will continue to receive routine care and undergo several study follow-up examinations during the first 16 weeks. In this control group, patients are on a waiting list for the acupuncture treatment, which will be started at week 16 and continued until the final follow-up at week 24 using the same acupuncture treatment protocol being performed in the other study arm (see Fig. 1 and Table 1).

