**Optional points depending on the following Chinese medicine diagnoses**	
Cold invasion into meridians	Moxa on EX-LE-10 Bafeng, KI 3
Deficiency of qi and xue	ST 36, GB 39, ST 41 (in pronounced sensory ataxia)
Qi-stagnation and blood stasis	GB 34, GB 40, SP 4
Wind and phlegm block channels	ST 36, SP 9, SP 4
Phlegm and heat block channels	SP 9, SP 10, GB 40, KI 7

Furthermore, at least 2 of 10 facultative acupuncture points will be selected according to the patient’s individual constitution and disease pattern following the diagnostic principles of Chinese medicine {11b}. The acupuncture points used in a session will be documented each time. A diagnosis of traditional Chinese syndrome at baseline is mandatory, and the diagnosis will be documented. Patients will lie down in supine position. Needles will be inserted perpendicularly and stimulated only in the beginning to achieve a DeQi sensation and then will be left in place without further stimulation for 20–25 min.

The duration of 12 acupuncture sessions within one treatment cycle with 1–2 sessions per week and between 20 and 30 min per session is supported by common textbooks for acupuncture and taught in acupuncture schools internationally. The needle length and diameter will be chosen according to the anatomical location and constitutional picture. If numbness is present, superficial puncture with a sharp needle will be carried out at the Bafeng points, and tiny amounts of blood will be released twice during the treatment period. In both groups, moxibustion is allowed and will be applied by using a common moxibustion TDP- lamp (Phoenix Bio TDP CE005) exclusively at the feet over 15 min at 20 cm distance to the toes, in case of cold and numb feet. Since the focus is on body acupuncture, we excluded auricular acupuncture strategies.

The patients in the control group will not receive acupuncture treatment for a period of 16 weeks after randomization. During this period, the patients in the control group will participate in follow-ups only with the use of diaries and questionnaires. After 16 weeks, the patients in this group will receive the same acupuncture treatment according to the principles described above.

The patients in both groups will be allowed to continue routine care medication (if applicable), which will be adapted as needed during the study.

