### Outcomes {12}

The primary outcome parameter in the ACUDPN study is the overall DPN-related complaints at week 8 measured on a 0–100 mm VAS (0 = no complaints, 100 = worst imaginable complaints).

The VAS is a well-established and validated assessment tool that has been used in several clinical studies in conventional medicine and complementary medicine, e.g., acupuncture [11, 17], as a primary or secondary outcome measure.

Responders to the study intervention will be defined as patients with an overall change in DPN-related complaints of 15 mm or more between the VAS at baseline and the VAS in week 8.

The secondary outcome measures include the overall number of DPN-related complaints at week 16 and week 24 (VAS); the pain intensity at weeks 8, 16, and 24 (VAS); and the Neuropathic Pain Symptom Inventory (NPSI) score at weeks 8, 16, and 24. The NPSI scores subdimensions of neuropathic pain, such as spontaneous ongoing or paroxysmal pain, evoked pain (i.e., mechanical and thermal allodynia/hyperalgesia), and dysesthesia/paresthesia, using an 11-point scale [18].

Since numbness is not assessed in the NPSI, we added the 11-point NRS scale for numbness (0 = no numbness at all to 10 = no sensation on the soles of the feet).

The Diabetic Peripheral Neuropathic Pain Impact (DPNPI) measure is a validated tool used to assess the disease-specific impact on the quality of life [19] and will be applied at the abovementioned time points in addition to a general health-related quality of life assessment using the SF-12 [20].

The German questionnaire on emotional pain perception *Schmerz Empfindungs Skala* (SES) will be used to monitor the effect of acupuncture on the affective components of pain [21] following a timely schedule as described above, i.e., at baseline and weeks 8, 16, and 24.

The Patient Global Impression of Change (PGIC) scale consists of a patient assessment from 0 = much worse to 7 = much better [22] and will be measured only at weeks 8, 16, and 24.

Further secondary outcome parameters are the general clinical and neurological presentation registered with the Neuropathy Deficit Score (NDS) [23] and the clinical Total Neuropathy Score (cTNS) [24]; these assessments will be noted as described above at baseline and weeks 8, 16, and 24. Adverse events, dropouts, withdrawals, and the respective reasons will be documented.

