Acupuncture practiced according to the principles of Chinese medicine is an individualized therapy [29]. In the ACUDPN study, we use a semi-standardized treatment protocol that is similar to the treatments applied in several other previous studies, including the ART and the ACUSAR studies [30–34].

Compared to previous studies investigating acupuncture for the treatment of DPN, the ACUDPN study uses additional acupuncture sessions and applies a more rigorous methodology, including validated questionnaires and neurophysiological parameters, with a longer follow-up period to assess the long-term effects.

In conclusion, the results of the ACUDPN study will have an impact on the decision of whether acupuncture might be considered an effective and safe therapeutic option for the treatment of DPN and whether acupuncture can exert neuroregenerating effects.

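### The week-24 between-arm analyses compare immediate with delayed acupuncture, not acupuncture with routine care alone, because the control arm is treated from week 16 to week 24

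*Protocol article*

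**What the plan says.** On the analysis, Statistical methods {20a} states: "The secondary outcomes will be analyzed similarly with an ANCOVA or logistic regression". The model contains treatment group (acupuncture or control), study centre and, where there is one, the baseline value. The same section calls everything beyond the primary analysis exploratory, with no multiplicity adjustment.

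On the time points, Outcomes {12} states: "The secondary outcome measures include the overall number of DPN-related complaints at week 16 and week 24 (VAS"). It also places pain VAS, NPSI, DPNPI, SF-12, SES, PGIC, NDS and cTNS at week 24, and the abstract adds sural nerve conduction.

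On treatment of the control arm, Study setting {9} gives the arrangement as: "waiting list for the acupuncture treatment, which will be started at week 16 and continued until the final follow-up at week 24". The regimen is to be identical to that of the acupuncture arm. Study intervention {11a}, in the text after Table 2, agrees: "The patients in the control group will not receive acupuncture treatment for a period of 16 weeks after randomization", and then "After 16 weeks, the patients in this group will receive the same acupuncture treatment according to the principles described above".

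On the question asked, Objectives {7} and Trial design {8} set acupuncture added to routine care against routine care by itself. The Discussion describes the trial as one "with a longer follow-up period to assess the long-term effects".

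**The concern.** Read together, these sections fix an analysis that cannot deliver the stated contrast at one of its time points. At week 24 no arm is on routine care alone. The controls are at the end of their course, and the acupuncture arm finished its own 16 weeks before. A group coefficient and p value from the acupuncture/control model would still be produced for each week-24 outcome. Nothing in the text tells the reader that they answer a different question from the same coefficient at weeks 8 and 16.

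What is at stake is the reading of durability. The abstract describes an 8-week intervention with 16 weeks of follow-up and does not mention the delayed treatment. A small or negative week-24 difference could be taken to mean that the benefit had worn off, when it may only mean that the controls had caught up.

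**Working it through.** **Timeline.** A course is 12 sessions over 8 weeks (Study intervention {11a}).
- Acupuncture arm: treated in weeks 0 to 8, so week 24 is 24 − 8 = 16 weeks after the end of treatment.
- Control arm: treated from week 16, and 16 + 8 = 24, so week 24 is the end of treatment.
- The last visit with an untreated control arm is week 16, which is 16 − 8 = 8 weeks after the acupuncture arm stopped.

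**The plan's own figure.** Sample size {14} gives a 15 mm difference, SD 25 mm, two-sided alpha 0.05 and 80% power, and arrives at 45 per group. The standardised difference is 15/25 = 0.6. The two-sample t test needs 44.6 per group, rounded up to 45, and power at 45 is 80.4% (81.2% by the normal approximation). The 90 reproduces, so 15 mm, 25 mm and 45 per arm are used below.

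**Expected week-24 contrast.** Let p be the share of the 15 mm that the acupuncture arm still has at week 24, and c the share that the control arm has reached. The documents give neither, so both are assumptions shown over a range. Any change under routine care common to both arms cancels.
- Benefit over routine care alone, the stated question: 15p.
- What the group term estimates: 15p − 15c = 15(p − c).
- Shortfall: 15p − 15(p − c) = 15c, whatever the value of p.

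Positive values favour acupuncture (mm):

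| p | 15p | 15(p − c), c = 50% | 15(p − c), c = 100% |
|---|---|---|---|
| 100% | 15 | 7.5 | 0 |
| 75% | 11.25 | 3.75 | −3.75 |
| 50% | 7.5 | 0 | −7.5 |
| 25% | 3.75 | −3.75 | −11.25 |
| 0% | 0 | −7.5 | −15 |

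**Chance of a significant result.** The standard error is 25 × √(2/45) = 5.27 mm. This carries the planning SD over to week 24 and ignores any gain from baseline adjustment. By the normal approximation:
- c = 100%: the chance of significance in favour of control is 2.5%, 11%, 30%, 57% and 81% for p = 100, 75, 50, 25 and 0%. The chance in favour of acupuncture is 2.5% at p = 100%, 0.4% at p = 75%, and below 0.1% at lower p.
- c = 50%: at p = 100% the chance in favour of acupuncture is 30%, against 81% for the full 15 mm. At p = 0% the chance in favour of control is 30%.

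The week-24 contrast equals the stated one only at c = 0, that is, if the delayed course does nothing.

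**The case against.** Much can be said for the plan. The only confirmatory test is the week-8 VAS, and the exploratory label covers every affected analysis. The waiting-list design is described openly. A randomised contrast of immediate with delayed treatment is valid in itself, so the model is not at fault, only what its group term is taken to mean. Since the secondary analyses follow the primary, adjusted means with confidence intervals in each arm are already planned output. The article is condensed, Fig. 1 and Table 1 are not shown, and an analysis plan might treat week 24 separately.

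The limits on weight stand. The defence of the text does not. The exploratory label deals with multiplicity and does not change what a coefficient estimates. The article states a method for all secondary outcomes, and an analysis plan that treated week 24 differently would have to depart from it. This is therefore more than a detail left out.

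Three stronger readings are not supported:
- A reader might infer that an effective treatment is bound to look null or reversed at week 24. That needs the controls to have reached the full effect. At c = 50% with full persistence the contrast still favours acupuncture, by 7.5 mm.
- A reader might infer that the Discussion claims a randomised long-term comparison with routine care. It speaks only of longer follow-up and long-term effects, and names no comparator.
- A reader might suspect that the control arm's week-16 data are also affected. Study intervention {11a} starts their acupuncture only after 16 weeks, so the text shows no such problem.

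**Conclusion.** The point holds, with limited reach. As written, the week-24 group comparison does not estimate the contrast named in the objectives, and it understates the benefit over routine care by 15c mm on the planning effect: 7.5 mm at c = 50% and 15 mm at c = 100%. The expected result can be attenuated, null or reversed while acupuncture works. Which of these occurs depends on p and c, for which the documents give no figures. The calculation also assumes that the 15 mm planning effect is true and that the delayed course acts as the immediate one does.

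The primary analysis, the sample size and the week-8 and week-16 secondary comparisons stand. The correction should be made before analysis, but the trial's main conclusion does not depend on it.

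**What to change.** - In Outcomes {12} and Statistical methods {20a}, limit between-arm comparisons of acupuncture with routine care to weeks 8 and 16.
- At week 24, report results within each arm as descriptive: the course from week 8 to week 24 in the acupuncture arm, and from week 16 to week 24 in the control arm. If a between-arm contrast is kept, label it *immediate versus delayed acupuncture* wherever it is reported.
- In the Discussion, state that follow-up controlled against routine care ends at week 16.

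The cost is wording only. No visit, treatment or sample size changes. The small downside is that no week-24 p value against routine care is reported, and the design cannot supply one in any case. The within-arm results cannot separate a treatment effect from the natural course of symptoms, hence the descriptive label.

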#### Interim analysis {21b}

An interim analysis is not planned. If the study has to be discontinued, the interim results will be accessible only to the principal investigators, who will make a decision regarding publication.

#### Methods for additional analyses {20b}

A subgroup analysis is planned to determine the effects of acupuncture on the subdimensions of neuropathic dysesthesias, such as tingling, numbness, and pain.

#### Methods applied in the analysis to address protocol nonadherence and any statistical methods applied to address missing data {20c}

The analysis will be performed with the full analysis set (FAS) based on an intention to treat (ITT). Missing values will not be replaced. Further analyses will be regarded as explorative (without adjustment and multiple imputation).

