In addition, the patients will be requested to complete patient diaries following a daily schedule, which will include recording on-demand medication use, a weekly assessment of the average VAS score of pain, and the overall number of DPN-related complaints during the first 8 weeks and at weeks 15 to 16 and 23 to 24.

The neurophysiological parameters will include measurements of the sural nerve. This nerve is pathognomonically affected in diabetic neuropathy and is used to monitor peripheral neuropathy. The nerve conduction velocity and amplitude of sensible action potentials will be measured with a novel point-of-care nerve conduction device (POCD) produced by NeuroMetrix™, Texas. This device is used in the DPNCheck®, which provides accurate, cost-effective, and quick screening data for the diagnosis and monitoring of diabetic peripheral neuropathy (DPN). With a 10-s period of measurement, this device can provide the numeric values of velocity (m/s) and amplitude (μV). This device has been validated in several studies as an accurate screening and monitoring instrument for DPN and the evaluation of the risk of diabetic foot [25–27].

TCM-related indexes as outcomes are not used in this trial.

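### The primary analysis is labelled ITT but omits every patient without a week-8 VAS, so arm-specific, symptom-related dropout can bias it in either direction, and no missing-data analysis is named

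*Protocol article*

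**What the plan says.** All references are to the protocol article.

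- **Statistical methods {20a}.** The primary endpoint is the change in the overall-complaints VAS from baseline to week 8. It is analysed by ANCOVA with group, centre and baseline VAS. The analysis set is called FAS and described as ITT-based, "thus evaluating each patient in the treatment group at random without the replacement of missing values".
- **Missing data {20c}.** The rule is repeated: "Missing values will not be replaced. Further analyses will be regarded as explorative (without adjustment and multiple imputation").
- **Sample size {14}.** "To account for a dropout rate of approximately 15%, 110 patients must be randomized". The evaluable number behind this is 90.
- **Outcomes {12}.** The patient diary includes "a weekly assessment of the average VAS score of pain, and the overall number of DPN-related complaints during the first 8 weeks", and again around weeks 16 and 24.
- **Blinding {17a} and Study setting {9}.** Patients know their allocation, and controls wait until week 16 for acupuncture.
- **Sections {11c}, {18a} and {18b}.** Patients are telephoned about missed visits or late questionnaires, missing items are chased by mail, and patients who stop treatment are encouraged to keep returning questionnaires.

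**The concern.** With one outcome time and no replacement, the model can use only patients who have a week-8 VAS. The set analysed is therefore the week-8 completers, which is not what the ITT label conveys. Inflating the sample for dropout protects power but does nothing for comparability.

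One arm attends 12 sessions in 8 weeks; the other waits. Patients in the two arms may leave for different reasons, and those reasons may be tied to how their symptoms develop. If so, the completers are no longer a randomised comparison, and the error falls on the trial's only confirmatory test. The diary may hold post-baseline scores for some of those who leave, but the stated analysis makes no use of them. No mixed model, imputation or missing-data sensitivity analysis is named.

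**Working it through.** **1. The plan's own figure.** Inputs from Sample size {14}: difference 15 mm, SD 25 mm, two-sided alpha 0.05, power 80%.

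- Normal approximation: n per arm = 2 × (1.96 + 0.84)² × (25/15)² ≈ 43.6, so 44. The t test gives 44.6, so 45 per arm, with power 80.4%. The stated 90 reproduces.
- Dropout: 90 / (1 − 0.15) = 105.9, so 106. The stated 110 is a conservative rounding that tolerates 20/110 = 18.2% loss.
- At 15% loss, 110 × 0.15 = 16.5 patients leave the primary analysis and 93.5 remain. Power by the t test is about 82%. The issue is bias, not power.

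**2. Bias formula.** Let d be the share missing in an arm, and g the amount (mm) by which the missing patients' mean week-8 VAS exceeds the completers' mean. The arm mean over all patients is the completer mean + d × g. The completer difference therefore overstates the benefit of acupuncture by

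bias = d_A × g_A − d_C × g_C.

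The gaps below are assumptions; the protocol gives none.

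| d_A, d_C | g_A, g_C (mm) | Bias in favour of acupuncture (mm) |
|---|---|---|
| 0.15, 0.15 | 15, 15 | 2.25 − 2.25 = 0 |
| 0.15, 0.15 | 15, 0 | +2.25 |
| 0.15, 0.15 | 25, 0 | +3.75 |
| 0.15, 0.15 | 0, 15 | −2.25 |
| 0.15, 0.15 | 15, −15 | 2.25 + 2.25 = +4.5 |
| 0.20, 0.10 | 15, 15 | 3.0 − 1.5 = +1.5 |
| 0.10, 0.20 | 15, 15 | 1.5 − 3.0 = −1.5 |

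**3. Simulation.** Each scenario had 3,000 trials of 55 per arm, SD 25 mm, ANCOVA on baseline and centre. Assumed: correlation 0.5 between baseline and later scores, 0.7 between a mid-treatment diary score and week 8, and about 15% missing per arm under no effect. Symptom-related dropout depends on the mid-treatment score. Complete cases were compared with multiple imputation using that diary score.

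| Who leaves | No true effect: complete-case estimate | Type I error | True effect 15 mm: complete-case estimate |
|---|---|---|---|
| At random in both arms | −0.1 mm | 5.5% | 14.95 mm |
| Poor responders in both arms | +0.1 mm | 5.1% | 14.33 mm |
| Poor responders in acupuncture, random in control | +2.1 mm | 7.4% | 16.58 mm |
| Poor responders in control, random in acupuncture | −2.1 mm | 8.2% | 12.86 mm |
| Opposite: poor responders in acupuncture, good responders in control | +4.4 mm | 16.4% | 18.72 mm |

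Imputation stayed within about 0.2 mm of the truth in every row, with type I error of 5.0-5.8%. That is a best case, because dropout depended only on a diary score that was always available. The Monte Carlo error on a 5% rate is √(0.05 × 0.95 / 3000) = 0.4 percentage points, so 7.4% and 8.2% should be read as similar.

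**The case against.** **The bias is not established.** The protocol gives no dropout reasons and no rates by arm. Complete-case ANCOVA is unbiased if missingness depends only on arm, centre and baseline, and nearly so if the mechanism is the same in both arms. A reader might infer that the rule inflates the acupuncture effect. The documents do not support that: losing the worst controls works against acupuncture by a similar amount. This stands, and the claim is limited to possible bias in either direction.

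**Stopping treatment is not the same as a missing outcome.** The week-8 VAS can be returned by mail, it is chased by telephone, and the travel reimbursement is paid only after the final questionnaire. If half of the acupuncture poor responders who stop still returned it (an assumption), a similar simulation gave about 1.0 mm and 4.9% type I error. This also stands: the retrieval steps reduce the problem. They do not analyse what remains missing, and the sample size still allows for about 15%.

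**The rule leaves room for sensitivity analyses.** It would be too strong to say that none is possible. A mixed model replaces no values, and further exploratory analyses are allowed. The phrase about multiple imputation in {20c} closely resembles the one about multiple testing in {20a}, so its meaning is uncertain. The unseen SAP may add analyses. But the no-replacement rule for the primary analysis is stated twice, so it is not a detail left open for the SAP.

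**The diary may not help.** It would also be too strong to say that each patient's course before dropout is known. Diaries are kept at home and mailed back, and those of dropouts may never arrive. The diary item is worded much as {20a} words the primary VAS, so reading it as the same scale is reasonable, but this should be confirmed on the form.

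**Conclusion.** The point holds as a risk, not as a demonstrated bias. The primary analysis is a complete-case analysis under an ITT label, and nothing named in the protocol shows how far its result depends on the missing patients. Against a 15 mm target, the bias is about 2 mm for or against acupuncture with type I error of about 7-8% when symptom-related dropout occurs in one arm only. It is up to about 4.5 mm and 16% when the mechanisms are opposite. With the same mechanism in both arms it is about 0 mm under no effect, and about 0.7 mm (15 − 14.33) against acupuncture at a 15 mm effect. These sizes rest on assumed mechanisms, gaps and correlations, and on dropout near the planned 15%. The 18.2% is the loss that 110 tolerates, not the rate the plan expects. Successful retrieval of week-8 questionnaires would make the bias smaller.

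**What to change.** Amend {20a} and {20c} before unblinding so that the week-8 contrast is estimated for all randomised patients, by one of:

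- a likelihood-based repeated-measures model on the weekly diary and week-8 overall-complaints VAS, with treatment, centre, baseline, week and treatment-by-week; or
- the same ANCOVA after multiple imputation by arm, using whatever diary scores are available.

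Preferably make this the primary analysis and keep the complete-case ANCOVA as a sensitivity analysis. At minimum, pre-specify it as a sensitivity analysis. In either case add a delta-adjusted analysis that makes missing acupuncture patients progressively worse, because the diaries of dropouts may be missing too. Describe the complete-case analysis as such rather than as ITT, and clarify the multiple-imputation phrase in {20c}.

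No new data are needed. The costs are a missing-at-random assumption (which the delta analysis probes), modest programming, and an amendment that must go to the ethics board. The timing is workable: at the reported status 62 patients were included, no interim analysis is planned and the statisticians are blinded. Made after unblinding, the same change would look data-driven.
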